| 103816 | 8CE0100 | Insulin alert patient information booklet given | 2 |
| 103817 | 8BAj.00 | Informed dissent not to carry insulin passport | 2 |
| 103902 | C10FG11 | Type II diabetes mellitus with arthropathy | 2 |
| 104254 | 7L10011 | Subcutaneous infusion with insulin pump | 2 |
| 104323 | C10F511 | Type II diabetes mellitus with gangrene | 2 |
| 104374 | 67D8.00 | Provision of diabetes clinical summary | 2 |
| 104453 | 66At011 | Type 1 diabetic dietary review | 1 |
| 104639 | C10FF11 | Type II diabetes mellitus with peripheral angiopathy | 2 |
| 104858 | 8BAm.00 | Insulin passport checked | 2 |
| 105302 | K08yA00 | Proteinuric diabetic nephropathy | 2 |
| 105337 | C10E811 | Type I diabetes mellitus - poor control | 1 |
| 105446 | 679c.00 | Insulin administration education | 2 |
| 105585 | 8CMW700 | Diabetes clinical pathway | 2 |
| 105740 | 2G5d.00 | O/E - Left diabetic foot at increased risk | 2 |
| 105741 | 2G5e.00 | O/E - Right diabetic foot at increased risk | 2 |
| 105784 | C109912 | Type 2 diabetes mellitus without complication | 2 |
| 106061 | C10FP11 | Type II diabetes mellitus with ketoacidotic coma | 2 |
| 106269 | 9m0..00 | Diabetic retinopathy screening administrative status | 2 |
| 106328 | 9m07.00 | Excluded diabetc retinop screen as under care ophthalmolgist | 2 |
| 106329 | 9m08.00 | Excluded from diabetic retinopathy screening as blind | 2 |
| 106332 | 9m00.00 | Eligible for diabetic retinopathy screening | 2 |
| 106360 | K27y700 | Erectile dysfunction due to diabetes mellitus | 2 |
| 106445 | 9m0E.00 | Excluded from diabetic retinopathy screen physical disorder | 2 |
| 106528 | C10FN11 | Type II diabetes mellitus with ketoacidosis | 2 |
| 106679 | 8OA3.00 | Provision of written information about diabetes and driving | 2 |
| 106722 | 9Oy0300 | Diabetic foot screening invitation second letter | 2 |
| 106723 | 9Oy0200 | Diabetic foot screening invitation first letter | 2 |
| 106738 | 9Oy0000 | Diabetic foot screening invitation | 2 |
| 106778 | 9m0C.00 | Excluded frm diabetic retinopathy screen as terminal illness | 2 |
| 107331 | 66AH100 | Conversion to insulin in secondary care | 2 |
| 107361 | 679L200 | Education about diabetes and driving | 2 |
| 107423 | 661N400 | Diabetes self-management plan review | 2 |
| 107452 | 66o..00 | Further diabetic monitoring | 2 |
| 107464 | 66AS000 | Diabetes Year of Care annual review | 2 |
| 107508 | 66AH200 | Conversion to insulin by diabetes specialist nurse | 2 |
| 107597 | 9m0D.00 | Excluded from diabetic retinopthy screen as learn disability | 2 |
| 107701 | C10FK11 | Hyperosmolar non-ketotic state in type II diabetes mellitus | 2 |
| 107739 | 679L211 | Advice about diabetes and driving | 2 |
| 107793 | 9Oy0400 | Diabetic foot screening invitation third letter | 2 |
| 107881 | K08yA11 | Clinical diabetic nephropathy | 2 |

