Primary outcomes: Data will be analysed for changes in all-cause mortality and CHD and stroke clinical events, diabetes diagnosis and chronic kidney disease (CKD) diagnosis. The Read codes used to identify cases of CHD in CPRD data will be those listed in reference 9. The Read codes used to identify cases of stroke in CPRD data will be those listed in reference 10. (9, 10) , while ICD-10 codes will be used in HES data. Where feasible stroke will be classified as haemorrhagic or ischaemic. CHD events will be classified as angina, myocardial infarction, coronary artery bypass surgery or percutaneous coronary intervention and other. To identify cases of diabetes, diabetes drug prescriptions will be analysed by mapping drug codes to chapter subheadings in the British National Formulary (6.1 for drugs used in diabetes). Medical diagnosis codes and levels of HbA1c levels (6.5%) will be analysed as well to identify diabetes diagnosis. Medical diagnosis codes and levels of serum creatinine will be used to identify CKD cases. (11) . Details of proposed case definitions are given in Table 1.

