**Table 1: Case definitions for key measures:**

| **Condition** | **Read Codes** | **Therapy Codes** | **Test results** | **ICD-10 codes** |
| --- | --- | --- | --- | --- |
|  |  |  |  |  |
| **Ischaemic heart disease** | As listed in reference 9. | N/A | N/A | I20-I25 |
|  |  |  |  |  |
| **Stroke** | As listed in reference 10. | N/A | N/A | I60-I64 |
|  |  |  |  |  |
| **Diabetes mellitus** | As listed in Appendix 1. | BNF chapter 6.1.1 and 6.1.2 | HbA1c >=6.5% (48 mmol/mol) | E10-E14 |
|  |  |  |  |  |
| **Chronic kidney disease** | K05 and K06 codes | N/A | eGFR based on serum creatinine using CKD-EPI equation (11) | N18, N19 |
|  |  |  |  |  |

Secondary outcomes: CVD risk and CVD risk factors, including: smoking, BP, total cholesterol, HDL and BMI. Data on medication prescription for antihypertensive drugs, lipid-lowering drugs, antiplatelet drugs and nicotine replacement therapy will be analysed by recording drug codes to chapter subheadings in the British National Formulary (chapter 2 for CVD drugs).

1. **Data/ Statistical analysis**

The proportion of participants with values recorded for five risk factors (blood pressure, total cholesterol, HDL, BMI and smoking status) will be evaluated. Risk factor values will also be assessed. Changes over time in prescription of drugs for CVD risk management, including antihypertensive, lipid-lowering, antiplatelet and nicotine replacement therapy, will be evaluated.

The association between NHSHC and changes in CHD, stroke, diabetes and CKD clinical events will be examined using Cox hazard and Poisson regression models. Person-time approach will be adopted, where the start date is the date of the check. Hazard ratios will be estimated using Cox proportional hazards models and incident rate ratio using Poisson regression model. The proportional hazard assumptions will be tested. Linear mixed models will be used to study changes in continues outcomes (BP, cholesterol and BMI measurements). Follow-up will be censored if a control participant receives a health check at a later date. The effect of deprivation will be evaluated. Potential effect modification from deprivation category will be evaluated by testing for an interaction of health check status and deprivation category.

1. **Plan for addressing confounding**

To control for potential cofounders, model covariates will include age, gender, ethnicity and deprivation indices.

1. **Plan for addressing missing data**

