Recording of risk factor values is an outcome of importance in respect of evaluating NHS health checks. Prescriptions, clinical events and deaths that are not recorded will be presumed to be absent, because recording of these measures is expected to be complete.

1. **Limitations of the study design, data sources and analytical methods**

A randomised evaluation would provide the optimal study design but as health checks are part of a national policy, the present non-randomised design will offer an achievable study design. We expect a high level of completeness for recording of NHS health checks because use of mandated Read codes is used for reimbursement of practices. We acknowledge that there may be lack of standardisation of blood pressure measurements and recording of measures such as smoking and body mass index may be subject to misclassification. Use of diagnostic codes for CVD events varies between general practices and some clinical events are recorded with codes that lack precision.

1. **Patient or user group involvement (if applicable)**

Patients have not contributed to the development of this protocol but we have engaged with patients in our health check evaluation work and will be able to discuss the results of this study with patient groups.

1. **Plans for disseminating and communicating study results, including the presence or absence of any restrictions on the extent and timing of publication**

The results of this study will be reported in national public health events and we will also prepare peer review paper for publication. It will also contribute to a PhD thesis.

1. **References**

| Medcode | ReadCode | ReadTerm | Type |
| --- | --- | --- | --- |
| 506 | C100112 | Non-insulin dependent diabetes mellitus | 2 |
| 608 | 66A2.00 | Follow-up diabetic assessment | 2 |
| 711 | C10..00 | Diabetes mellitus | 2 |
| 758 | C10F.00 | Type 2 diabetes mellitus | 2 |
| 1038 | C100011 | Insulin dependent diabetes mellitus | 1 |
| 1323 | F420.00 | Diabetic retinopathy | 2 |
| 1407 | C10FJ00 | Insulin treated Type 2 diabetes mellitus | 2 |
| 1549 | C10E.00 | Type 1 diabetes mellitus | 1 |
| 1647 | C108.00 | Insulin dependent diabetes mellitus | 1 |
| 1682 | C101.00 | Diabetes mellitus with ketoacidosis | 1 |
| 1684 | 66A4.00 | Diabetic on oral treatment | 2 |
| 2340 | F381311 | Diabetic amyotrophy | 2 |
| 2342 | F372.12 | Diabetic neuropathy | 2 |
| 2378 | 66AJ.00 | Diabetic - poor control | 2 |

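### Diabetes and CKD can become primary-outcome events on unconfirmed test results, so event counts rise with testing and the hazard and rate ratios may be biased upwards by an unknown amount

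*Protocol*

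**What the plan says.** Under Exposures, Outcomes and Covariates the primary outcomes are set out: "Data will be analysed for changes in all-cause mortality and CHD and stroke clinical events, diabetes diagnosis and chronic kidney disease (CKD) diagnosis". For diabetes, after prescriptions, the text adds: "Medical diagnosis codes and levels of HbA1c levels (6.5%) will be analysed as well to identify diabetes diagnosis". For CKD it says: "Medical diagnosis codes and levels of serum creatinine will be used to identify CKD cases". It then points to the table: "Details of proposed case definitions are given in Table 1".

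Table 1 has columns for Read codes, therapy codes, test results and ICD-10 codes. The test-result entries are:

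- Diabetes: "HbA1c >=6.5% (48 mmol/mol".
- CKD: "eGFR based on serum creatinine using CKD-EPI equation (11". This names an equation but no eGFR value that would make a case.

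Neither entry gives a number of values, an interval or a need for support from another column. Nothing says whether the columns are alternatives or must be combined.

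Three other provisions bear on the point. Under Data/Statistical analysis: "Person-time approach will be adopted, where the start date is the date of the check". Under the plan for missing data: "Prescriptions, clinical events and deaths that are not recorded will be presumed to be absent, because recording of these measures is expected to be complete". Under the plan for confounding, the covariates are age, gender, ethnicity and deprivation.

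**The concern.** If the columns are alternatives, which is the natural reading of the words on HbA1c, one value at or above 6.5% makes a diabetes event. For CKD, whatever cut-off is chosen, nothing makes the finding chronic. A value that crosses a line once through measurement variation or a passing illness then counts as incident chronic disease.

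Under such a rule the chance of at least one qualifying value grows with the number of tests. A person never tested can become a case only through a code or a prescription, and otherwise is presumed free of disease. If one arm is tested more often, it collects more of these events. The model has no term for testing, and age, gender, ethnicity and deprivation cannot stand in for it.

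Objective 2 is that incidence may be lower after a health check. Excess test-defined events in the health-check arm would push the hazard and rate ratios upwards, and could hide a real reduction or make the check look harmful.

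**Working it through.** **The protocol's own figure.** The only design calculation is for CHD: 3 per 1,000 per year, risk ratio 0.85, 75,000 against 182,000, three years. With risks 0.003 × 3 = 0.009 and 0.009 × 0.85 = 0.00765, two-sided 0.05, power is 92.7%, which agrees with the stated more than 90%. It is unaffected by this point. The protocol gives no figure for diabetes, CKD or testing frequency, so everything below rests on assumptions.

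**Step 1: accumulation with tests.** Let f be the chance that a person without the disease has a qualifying value on one test, with tests independent. The chance of at least one in k tests is 1 − (1 − f)^k.

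| f | k = 1 | k = 2 | k = 3 |
|---|---|---|---|
| 0.5% | 0.50% | 1.00% | 1.49% |
| 1% | 1.00% | 1.99% | 2.97% |
| 2% | 2.00% | 3.96% | 5.88% |

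**Step 2: what unequal testing would do.** Assume a true three-year risk p, all true cases found in both arms, two tests per health-check participant and one per control. Observed risk is 1 − (1 − p)(1 − f)^k. With p = 1%, f = 0.5% and no true effect:

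- health check: 1 − 0.99 × 0.995² = 0.01988
- control: 1 − 0.99 × 0.995 = 0.01495
- apparent risk ratio: 0.01988 / 0.01495 = 1.33

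Over p of 1% to 3% and f of 0.5% to 1%, the apparent ratio is 1.14 to 1.49 when the true ratio is 1, and 1.01 to 1.42 when the true ratio is 0.85. If every positive were retested in both arms and errors were independent, these would become 1.00 to 1.01 and 0.85 to 0.86. Step 3 shows why that last result is a best case.

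**Step 3: people near the threshold.** Real errors are not independent of the person: someone whose true level lies close to the line tends to cross it again. Simulation with a normal true level and proportional within-person variation gives the following. The means, SDs, CVs and the eGFR cut-off of 60 are all assumptions; the protocol states none of them.

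| Assumed scenario | Ever positive, 1 test | Ever positive, 3 tests | Rise | False share, any of 3 | False share, two of 3 |
|---|---|---|---|---|---|
| eGFR mean 88, SD 14, CV 6% | 2.75% | 4.27% | 1.55 | 48% | 20% |
| eGFR mean 85, SD 15, CV 8% | 6.03% | 9.65% | 1.60 | 51% | 22% |
| HbA1c mean 5.6%, SD 0.35, CV 2% | 0.77% | 1.44% | 1.87 | 66% | 35% |
| HbA1c mean 5.6%, SD 0.40, CV 3% | 2.07% | 3.98% | 1.92 | 71% | 40% |

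"False" here means a true level on the healthy side of the line. Requiring two qualifying values roughly halves the false share. When each positive is retested once, confirmed cases still rise about 1.4 to 1.9 fold from one to three testing occasions. Confirmation therefore improves specificity but leaves the dependence on testing largely in place.

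**The case against.** **No single-value rule is written.** Table 1 gives a threshold, not the words any or first, and calls its definitions proposed. Number of values, column logic and event date are often left to an analysis plan. This has some force. But the protocol presents Table 1 as the place where the details of the primary-outcome definitions stand, and the text adds HbA1c to codes and drugs as a further route to a case. Followed as written, one qualifying HbA1c suffices.

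**The CKD rule is incomplete rather than lax.** This stands. A reader might infer that any low eGFR counts as CKD, or that 60 is the cut-off. The protocol supports neither, since it states no cut-off. The CKD row lacks both a threshold and a persistence requirement.

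**Unequal testing is not documented.** This also stands. The five risk factors listed for analysis are blood pressure, total cholesterol, HDL, BMI and smoking. The Background says the check estimates risk of diabetes and CKD, not that HbA1c or creatinine is measured. More testing after a check is a reasonable inference from an exposure that assesses these risks, not a stated fact.

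**The simulated sizes depend on thin-tailed assumptions.** Correct. Adding an assumed 1% to 3% of people with true HbA1c above the line cuts the false share of single-test positives from 41–70% to 11–40%, and the one-to-three-test rise from 1.7–2.1 fold to 1.2–1.7 fold. Coded and treated cases would dilute the effect further. Many of the false positives (60–88% for HbA1c) have a true level within 0.2 points of the line, so calling them free of disease is too strong.

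**A second test is itself testing.** Correct, and it changes the remedy: confirmation alone is not enough.

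**Conclusion.** The point holds. Two of five primary outcomes can be met by unconfirmed test results, the combination of columns is unstated, and the CKD row has no cut-off. That event counts then rise with testing is arithmetic and needs no assumption beyond a non-zero false-positive chance.

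The bias between arms is conditional. If testing is more frequent after a check, the hazard and rate ratios for diabetes and CKD are pushed upwards, against Objective 2, and no listed covariate corrects this. The ratios of 1.14 to 1.49 under no effect are illustrations under assumed testing and error rates, not estimates for this cohort.

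A reader might infer that the bias is established and large, or that a repeat-test rule would abolish it. The documents support neither: they give no testing frequency by arm, and confirmed counts still rise with testing. All-cause mortality, CHD and stroke are not touched, because they are not defined by test results. This should be changed before analysis; it does not invalidate the design.

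**What to change.** In Table 1:

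1. State whether the columns are alternatives or must be combined, for each condition.
2. State the eGFR cut-off used for the research case definition.
3. Require a test-only case to be supported by a second qualifying value, a diagnosis code or, for diabetes, a drug. For CKD, separate the two values by a prespecified interval that shows chronicity.
4. State how the event is dated, with the same rule in both arms.

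In the analysis section:

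5. Add a sensitivity analysis limited to coded or treated diagnoses, which does not use test results to define a case.
6. Report HbA1c and creatinine testing rates by arm, so the reader can judge the likely direction and strength of bias.
7. Keep the single-value definition as a further sensitivity analysis.

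The cost is wording and some programming, with no change to the cohort or its matching. The main downside is fewer events: true cases tested once and never coded are missed, and this loss may itself differ between arms. That is why items 5 and 6 belong with item 3.

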A new programme of NHS Health Checks (NHSHC) was introduced in the UK in 2009. This aims to provide cardiovascular risk assessment every five years for adults aged 40-74 who are not already diagnosed with CVD or diabetes. The NHSHC offers a promising strategy for preventing CVD, yet several concerns have been raised in relation to its uptake, cost-effectiveness, success in reducing diseases and effectiveness of risk management. In this context, evaluation of the programme’s longer-term outcomes is crucial. This study aims at evaluating changes in risk and cardiovascular clinical events and mortality outcomes following uptake of a health check. We will use a matched cohort design in the CPRD by comparing participants with a record of a complete NHSHC between 1st of April 2010 and 31st of March 2013 with follow-up data available for a minimum of three years after their health check up to 31st March 2016, together with matched control participants who did not receive a health check. We will adopt a time-to-event framework with date of check as the start date to evaluate the onset of new prescriptions. Hazard ratios will be estimated using the cox proportional hazards model and incident rate ratios using Poisson regression to examine the association between the programme and changes in clinical events and mortality.

1. **Objectives, Specific Aims and Rationale**

**Aim:** To measure the long term outcomes of the NHS Health Checks programme and evaluate whether outcomes following an NHS Health Check are more favourable than in controls.

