Since the implementation of the NHS Health Check, studies have examined the effectiveness of the programme in terms of CVD risk reduction. Cochrane, Davey (6) monitored the changes in CVD risk factors after the first year of implementing the NHSHC and assessed the benefit of the lifestyle support component of the programme. They compared participants who received the health check alone with participants who received the health check together with additional lifestyle change support. The mean CVD risk declined in both groups. In the health check group, it was 32.9% at baseline and it reduced to 29.4% (p<0.001) after one year follow up. In the health check plus lifestyle support group CVD risk was 31.9% at baseline and it reduced to 29.2% (p<0.001) after one year follow up (6). Another study aimed at assessing the CVD risk reduction after one year follow-up (7). In participants who had a completed health check (n=1886) the mean global CVD risk score was reduced significantly from 28.2% (CI= 27.3,29.1) to 26.2% (CI= 25.4, 27.1)(7). Both studies showed modest reduction in CVD risk and CVD risk factors. However, participants were only followed after one year. Since the NHSHC was introduced in 2009, long term follow up would provide further assessment of the programme’s effectiveness, which this study aims to achieve.

The present analysis will draw upon our previous CPRD study on health checks (Protocol: 13_071A). (8) The previous study constructed a matched cohort design in which participants who had received health checks between 1 April 2010 and 31 March 2013 and who had at least 12 months records, were compared with controls who did not receive a health check. This previous study focused on risk factor detection and showed that health checks are associated with increased detection of hypercholesterolaemia, and to a lesser extent obesity and hypertension, but smokers may be under-represented among participants in the programme. The proposed study aims to evaluate longer term follow-up of substantive health outcomes. This study aims, therefore, to evaluate changes in risk factors, clinical events and mortality outcomes. In this proposed study, all individuals will have the potential to provide a minimum of three years of follow-up following the health check.

1. **Study Type**

The study will be hypothesis testing, estimating health check programme through a comparison of health check and control participants.

1. **Study Design**

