The original sample was extracted from the October 2014 release of CPRD for 140,356 participants with a record of an NHS Health Check between 1 April 2010 and 31 March 2013, from 452 general practices in England. We restricted the sample to all 106,784 participants registered with 334 general practices with IMD 2010 quintile for England, linked via the participant postcode, at the lower super-output area level. We also excluded all patients who were ever treated with antihypertensive drugs (8531) or statins (1529) before the date of the check. We also excluded patients (4859) who did not have a full year of up to standard record before the date of the check and one patient whose check was after 31 March 2013. We also excluded patients with diabetes (227), coronary heart disease (2) or stroke (3) diagnosed before the check. There remained 91,618 participants who had a health check between 1 April 2010 and 31 March 2013, who had at least 12 months record, were never treated with antihypertensive drugs or statins, and were not diagnosed with diabetes, stroke or CHD before the check. For these 91,618 participants, eligible control participants were identified for 75,123 (82%) and these participants, and their matched controls, will be included in the present study.

1. **Selection of comparison group(s) or controls**

Control participants were selected if they were eligible for the NHS Health Checks but did not receive the check, they might have been invited to attend the Health Check, or not. The control participants were individually matched by general practice, gender and age with participants who received the Health Check.

1. **Exposures, Outcomes and Covariates**

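### Nicotine replacement has no smoker at-risk group, and baseline smoking is neither matched nor listed for adjustment, so a whole-cohort comparison would be biased downward if attenders include fewer smokers

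*Protocol*

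**What the plan says.** All locations are in the Protocol.

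- **Outcome.** Exposures, Outcomes and Covariates lists nicotine replacement among the secondary outcomes, in one sentence with the cardiovascular drugs: "Data on medication prescription for antihypertensive drugs, lipid-lowering drugs, antiplatelet drugs and nicotine replacement therapy will be analysed".
- **Analysis.** Data/ Statistical analysis adds: "Changes over time in prescription of drugs for CVD risk management, including antihypertensive, lipid-lowering, antiplatelet and nicotine replacement therapy, will be evaluated". The Technical Summary gives the framework for prescriptions, a "time-to-event framework with date of check as the start date to evaluate the onset of new prescriptions". Neither section gives a separate population for nicotine replacement.
- **Population.** Sample Size carries forward the same 75,123 checked participants and 182,245 controls as the team's previous study.
- **Matching.** Selection of comparison group(s) or controls: "The control participants were individually matched by general practice, gender and age with participants who received the Health Check".
- **Adjustment.** Plan for addressing confounding: "model covariates will include age, gender, ethnicity and deprivation indices".
- **Unrecorded prescriptions.** Plan for addressing missing data: "Prescriptions, clinical events and deaths that are not recorded will be presumed to be absent".
- **Smoking imbalance.** Background, reporting the previous study: "smokers may be under-represented among participants in the programme".
- **Smoking data.** Smoking status is itself a study variable, among "CVD risk and CVD risk factors, including: smoking, BP, total cholesterol, HDL and BMI".

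**The concern.** Starting nicotine replacement presupposes smoking. A never-smoker is not at risk of this outcome in any useful sense, but under the missing-data rule would count as untreated if kept in the denominator. The Protocol applies at-risk reasoning to two other classes: Study Population removes anyone ever treated with antihypertensive drugs or statins before the check, so everyone left can have a first prescription. It has no equivalent step for nicotine replacement.

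This would matter little if the two arms contained the same share of smokers. The Protocol gives a reason to doubt that, from the same cohort, and neither matching nor the listed covariates would correct it. The Limitations section mentions misclassification of smoking but not this imbalance.

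Objective 1 tests whether cardiovascular risk management changes more after a check than in controls, and nicotine replacement is the only smoking treatment listed. A ratio that mixes smoking prevalence with treatment of smokers could lead the evaluation to miss a real benefit.

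**Working it through.** **The plan's own figure.** There is none for nicotine replacement. The only design calculation is for CHD: a three-year risk of 3 × 0.003 = 0.009 in controls, 0.85 × 0.009 = 0.00765 in checked participants, 75,000 against 182,000 people, and alpha 0.05 (taken as two-sided, since the Protocol does not say). This gives 92.7% power, in line with the stated figure of more than 90%. The present point does not depend on it.

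**Formula.** Let *s1* and *s0* be smoking prevalence in attenders and controls, and *q1* and *q0* the risk of starting nicotine replacement among smokers. If non-smokers do not start it:

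whole-cohort ratio = (*s1* × *q1*) / (*s0* × *q0*) = (*s1*/*s0*) × within-smoker ratio

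The observed ratio falls below 1 only when the within-smoker ratio is below *s0*/*s1*, the break-even value.

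**Inputs.** The Protocol gives neither smoking prevalences nor nicotine replacement rates, so every prevalence below is an assumption.

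| Attenders v controls | Factor *s1*/*s0* | Break-even *s0*/*s1* | True 1.0 shows as | True 1.2 | True 1.3 | True 1.5 |
| --- | --- | --- | --- | --- | --- | --- |
| 20% v 20% | 1.00 | 1.00 | 1.00 | 1.20 | 1.30 | 1.50 |
| 18% v 20% | 0.90 | 1.11 | 0.90 | 1.08 | 1.17 | 1.35 |
| 17% v 20% | 0.85 | 1.18 | 0.85 | 1.02 | 1.105 | 1.275 |
| 15% v 20% | 0.75 | 1.33 | 0.75 | 0.90 | 0.975 | 1.125 |
| 14% v 20% | 0.70 | 1.43 | 0.70 | 0.84 | 0.91 | 1.05 |
| 17% v 25% | 0.68 | 1.47 | 0.68 | 0.816 | 0.884 | 1.02 |

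**Sample size does not protect against this.** Take 17% v 20%, no true difference among smokers, and an assumed 10% of smokers starting nicotine replacement. Expected starts are 75,123 × 0.17 × 0.10 ≈ 1,277 and 182,245 × 0.20 × 0.10 ≈ 3,645. The standard error of the log ratio is about √(1/1,277 + 1/3,645) ≈ 0.0325, so the expected 95% interval around 0.85 is exp(−0.1625 ± 1.96 × 0.0325), about 0.80 to 0.91. The artefact would look like a precise finding.

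**After the fix.** Among smokers only, *s1*/*s0* drops out and the ratio is the within-smoker ratio.

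**The case against.** The strongest reply is that the all-participants denominator is inferred from silence. No section states a denominator for any drug class, and a statistical analysis plan could set one. That stands as far as it goes: a reader might infer that the Protocol states a whole-cohort comparison for nicotine replacement, and it does not. But the Protocol is not blank here. It fixes one cohort, describes nicotine replacement together with the other classes, starts follow-up at the check, counts missing prescriptions as absent, and names matching factors and covariates without smoking. Followed as written, that produces the whole-cohort comparison.

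Two stronger readings are tempting and unsupported:

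- *That smokers are under-represented among attenders.* The Background says only that they may be, and gives no prevalence.
- *That the check will appear to reduce smoking treatment.* This does not follow. With 18% v 20%, a true ratio of 1.30 still shows as 1.17, and with 17% v 20% any within-smoker increase above about 18% still shows as an increase.

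Two further replies have partial force. If change over time were compared within each arm on a ratio scale, a stable smoker fraction would cancel; the time-to-event analysis of new prescriptions in the Technical Summary is not that analysis. And the covariate list may not be exhaustive, so adjusting for baseline smoking would largely deal with the problem; but the Protocol does not name it.

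**Conclusion.** The point holds in a limited form. The Protocol leaves nicotine replacement without a smoker at-risk group and without matching or listed adjustment for baseline smoking, while reporting a possible smoking imbalance in the same cohort. If attenders do include fewer smokers, the whole-cohort ratio is scaled down by the ratio of prevalences: 0.90, 0.85 or 0.75 for assumed 18%, 17% or 15% against 20%. This can hide a real increase among smokers, and reverses it only when the increase is smaller than the prevalence gap.

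The conclusion rests on three assumptions: that essentially only smokers start nicotine replacement (any starts among non-smokers would soften the factor), that attenders include fewer smokers, and that the illustrative prevalences are plausible. With equal prevalences the factor is 1 and there is no bias from this source. One secondary outcome is affected; the primary outcomes are not. The change should be made, but the study does not stand or fall on it.

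**What to change.** State in Data/ Statistical analysis that nicotine replacement is analysed, in both arms, among people whose last smoking record strictly before the index date is current smoker. For a control, the index date is taken here to be the matched participant's check date. Report by arm the proportion with a smoking status recorded before that date.

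Records made at the check must be excluded. Recording of risk factors is itself an outcome of the check, so a same-day record would let the check define who is a smoker in one arm only, while controls relied on older entries.

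The cost is modest, because smoking status is already a study variable. At the assumed 17% and 20%, the analysis set would be about 75,123 × 0.17 ≈ 12,771 attenders and 182,245 × 0.20 = 36,449 controls, before losses for missing records. The non-smokers removed would contribute few or no starts, so the real loss is people with no earlier smoking record, who drop out of this one outcome. Earlier records may also be out of date for some people; the recording proportions by arm will help readers judge how far the restricted comparison can be trusted.
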